## Abstract

**Background:**

Entecavir and tenofovir disoproxil fumarate (TDF) are standard first-line treatments to prevent viral reactivation and hepatocellular carcinoma (HCC) in individuals chronically infected with the hepatitis B virus (HBV), but the long-term efficacy of the two drugs remains controversial. Also unclear is whether the drugs are effective at preventing viral reactivation or HCC recurrence after hepatectomy to treat HBV-associated HCC. This trial will compare recurrence-free survival, overall survival, viral indicators and adverse events in the long term between patients with HBV-associated HCC who receive entecavir or TDF after curative resection.

**Methods:**

This study is a randomized, open-label trial. A total of 240 participants will be randomized 1:1 into groups receiving TDF or entecavir monotherapy. The two groups will be compared in terms of recurrence-free and overall survival at 1, 3, and 5 years after surgery; adverse events; virological response; rate of alanine transaminase normalization; and seroreactivity at 24 and 48 weeks after surgery.

**Discussion:**

This study will compare long-term survival between patients with HBV-associated HCC who receive TDF or entecavir monotherapy. Numerous outcomes related to prognosis will be analyzed and compared in this study.

**Trial registration:**

ClinicalTrials.gov NCT02650271. Registered on January 7, 2016.

## Introduction

### Background and rationale

Chronic infection with the hepatitis B virus (HBV), which affects more than 290 million people worldwide [1], is one of the strongest risk factors for cirrhosis and hepatocellular carcinoma (HCC). Entecavir and tenofovir disoproxil fumarate (TDF) are widely recommended as standard first-line treatments capable of slowing progression of cirrhosis and reducing the risk of liver failure and onset of HCC [2, 3]. Some studies have shown that monotherapy with entecavir or TDF can significantly reduce viral load in plasma and improve liver function without eliciting drug resistance or serious adverse events [4–6]. In most parts of the world, generic formulations of both drugs are widely available at relatively low prices.

While strong evidence exists that either monotherapy can prevent viral reactivation and HCC in the short term, whether it does so in the long term is less clear. Stopping the medication leads in many cases to reactivation of HBV infection and increased risk of HCC, even in patients whose viral load or hepatitis B surface antigen has been undetectable for years [2, 3, 7]. We are unaware of any randomized studies examining the ability of entecavir or TDF to prevent cirrhosis or HCC in the long term in patients chronically infected with HBV, and the numerous prospective or retrospective cohort studies in the literature have come to divergent conclusions. For example, for patients receiving initial treatment, some studies found TDF to be significantly better than entecavir at preventing HCC [8–10], but other studies involving first- or second-line treatment found them to be similarly effective for this outcome [11–14]. Even meta-analyses have come to divergent conclusions: several indicated the superiority of TDF for preventing HCC [15–17], while another reported similar efficacy for the two drugs [18]. These considerations highlight the need for a large, rigorously designed trial to compare the two monotherapies with long follow-up.

Similarly, the literature is unclear about how well either monotherapy prevents viral reactivation or recurrence of HCC after patients with HBV-associated HCC have undergone curative hepatectomy. The drugs are often given prophylactically to such patients after hepatic resection in order to inhibit viral replication and thereby reduce risk of HCC recurrence. Indeed, we and others have shown that preoperative levels of HBV DNA or surface antigen HBsAg are associated with risk of HCC recurrence [19, 20], and that entecavir monotherapy can reduce this risk [21, 22]. Some retrospective studies [23, 24] and a meta-analysis [25] have shown TDF to protect against HCC recurrence better than entecavir, while other studies have concluded the two drugs to be similarly effective for this outcome [26, 27]. The above retrospective studies did not find differences between entecavir and TDF in virological response, serological reaction, or adverse reactions.

### Objectives

To clarify and compare the long-term efficacies of the two monotherapies, we have launched a randomized trial to compare monotherapy with entecavir or TDF for preventing viral reactivation and HCC recurrence in the short and long term after hepatic resection to treat HBV-associated HCC.

### Trial design

This study is a phase 3 randomized, open-label, superiority trial. Participants will be randomly divided into two groups in a ratio of 1:1, one of which will receive TDF monotherapy and the other will receive entecavir monotherapy during the peri- and postoperative period. The primary outcome of the study is the rate of recurrence-free survival at 1, 3 and 5 years after curative hepatectomy. The secondary outcomes are the rate of overall survival at 1, 3, and 5 years; adverse reactions; virological response; rate of alanine transaminase normalization; and seroreactivity at 24 and 48 weeks after surgery.

## Methods

### Study setting

This study will be conducted at the Guangxi Medical University Cancer Hospital, the First People’s Hospital of Qinzhou, and the Second Affiliated Hospital of Guangxi Medical University. These three hospitals are all located in Guangxi province, a high incidence area of HCC in China.

### Eligibility criteria

To be enrolled in the study, participants must be 18–75 years old, they must have tested positive for HBsAg and/or HBV DNA at admission, they must have undergone curative hepatectomy at one of the study sites, and their diagnosis of HCC must have been confirmed by postoperative histopathology. Curative resection is defined based on intra- and postoperative criteria [28]. Participants must also have scored 0 or 1 on the ECOG Performance Status Scale at admission. They must be aware of their condition and able to provide written consent.

Potential participants will not be enrolled if they tested positive at admission for antibodies against hepatitis C virus or human immunodeficiency virus, or if they were receiving any anti-HBV therapy before enrollment, such as interferon, entecavir, TDF, adefovir dioxide, or lamivudine. They will also be excluded if they have a history of other malignancies or serious diseases within the previous five years, a history of organ transplantation or drug allergy, autoimmune disease or history of long-term use of glucocorticoids. Pregnant or lactating women will not be considered for enrollment. Participants who fail to comply with treatment or complete follow-up will be excluded from the study.

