The primary outcome is recurrence-free survival, defined as the time between the randomization date and first occurrence of HCC recurrence, as detected by imaging. Recurrence can be extrahepatic or new intrahepatic. The secondary outcomes of this trial include overall survival, defined as the time between the randomization date and death. If the participant is alive at the end of the study or is lost to follow-up, the last follow-up visit will be used. Other secondary outcomes are virological response, defined as titer of HBV DNA; rate of alanine transaminase normalization; seroreactivity at 24 and 48 weeks after resection, defined as the presence of HBsAg or HBV e antigen; frequency of treatment-related adverse events, as assessed using the Common Terminology Criteria for Adverse Events (version 5.0) [32]; and treatment tolerability, measured in terms of the proportion of patients completing the planned treatment.

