#### Methods in analysis to handle protocol non-adherence and any statistical methods to handle missing data

Data analysis of this study will according to the intention-to-treat principle. Efforts are made to follow-up participants who dropped out from treatment in order to obtain more evaluation indexes and recorded in the CRFs. The last assessment data will be applied for patients who lost to follow-up.

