## Discussion

Entecavir and TDF are both standard first-line treatments for patients with chronic hepatitis B. However, the long-term efficacy of monotherapy with entecavir or TDF in preventing tumor recurrence for patients with HBV-related HCC after curative hepatectomy are still controversial and need to be further verified.

This study will analyze numerous outcomes related to prognosis, including adverse events, virological response, rate of alanine transaminase normalization, and seroreactivity. The results of this study will help to advance our understanding of the long-term efficacy of entecavir or TDF monotherapy. A randomized controlled trial with small sample size comparing the efficacy of TDF (*n* = 74) and entecavir (*n* = 74) monotherapy for patients with HBV-related HCC after curative treatment found TDF therapy was associated with a significantly lower risk of tumor recurrence than entecavir therapy [33]. Our randomized trial with large sample size will provide more stronger evidence about the efficacy of entecavir or TDF monotherapy for patients with HBV-related HCC after curative resection. In general, the larger the sample size and the longer the follow-up, the more reliable the results. We had planned to revise the reference [27] for the sample size calculation, expecting to enroll 638 cases, but did not get approval from the Ethics Committee of Guangxi Medical University Cancer Hospital. The Ethics Committee is of the view that since this study is not directly supported by sufficient funding, there is a risk that if the sample size is further expanded, it may not be successfully completed in accordance with the intended objectives.

A limitation worth noting is that participants will know their assigned treatment may lead some to request conversion of their treatment, triggering their exit from the study.

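### The eligibility section excludes participants for non-compliance or incomplete follow-up after randomisation, which contradicts the stated intention-to-treat analysis

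*Protocol article*

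**What the plan says.** **Eligibility criteria.** The exclusions open with conditions checked before entry: "Potential participants will not be enrolled if they tested positive at admission for antibodies against hepatitis C virus or human immunodeficiency virus". The paragraph closes with a different kind of rule: "Participants who fail to comply with treatment or complete follow-up will be excluded from the study".

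**Methods in analysis to handle protocol non-adherence and missing data.** Three statements keep the same patients in:
- The general principle is set first: "Data analysis of this study will according to the intention-to-treat principle".
- People who stop their drug are not abandoned, because observation is meant to continue and to be documented.
- Those who disappear from view also stay in the data set: "The last assessment data will be applied for patients who lost to follow-up".

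**Outcomes.** Directly after the definition of overall survival: "If the participant is alive at the end of the study or is lost to follow-up, the last follow-up visit will be used". The secondary outcomes also include "treatment tolerability, measured in terms of the proportion of patients completing the planned treatment".

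**Discussion.** As a limitation of the open-label design, the authors note that knowing the assigned drug "may lead some to request conversion of their treatment, triggering their exit from the study".

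**The concern.** Compliance with a long-term oral drug and completion of follow-up are known only after randomisation. Listing them as grounds for exclusion means that membership of the study depends on what happens under the allocated treatment. The analysis section promises the reverse, so a trial team cannot obey both.

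The primary comparison of recurrence-free survival is at stake. Randomisation protects it only if the patients compared are the patients randomised. Patients and investigators know the arm, and follow-up is planned for five years, so there is both time and opportunity for exits to differ between arms. If exit is related to prognosis and differs by arm, removing those patients distorts the comparison. If they are removed from follow-up as well as from the analysis, their later outcomes may not be recoverable.

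**Working it through.** **1. The passages side by side**

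| Patient | Eligibility criteria | Non-adherence section and Outcomes |
|---|---|---|
| Stops or does not comply with the drug | Excluded | Followed, recorded, analysed by intention-to-treat |
| Lost to follow-up | Excluded | Kept, using the last assessment or visit |
| Does not complete planned treatment | Excluded if this counts as failing to comply | Needed in the denominator of the tolerability outcome |

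The eligibility paragraph speaks of potential participants for the true entry criteria and of participants in the disputed sentence. That supports reading it as a rule for people already enrolled. If non-completers were excluded, the tolerability proportion would approach 100% by construction.

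**2. How many patients the plan itself expects**

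Inputs (Sample size section): 3-year recurrence-free survival 64% and 79%, 90% power, two-sided 0.05, two years' enrolment, five years' follow-up, 10% loss.
- Hazard ratio = ln(0.79)/ln(0.64) = 0.528.
- Events (Schoenfeld) = 4 × (1.960 + 1.282)² / (ln 0.528)², giving 104.
- With exponential survival, uniform accrual over 2 years and 7 years in total, the mean event probability is 0.482. Then 104/0.482 ≈ 216, or 108 per arm.
- 216/0.90 = 240.

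The stated sample size reproduces. The planned loss is 240 − 216 = 24 patients. One section excludes them and the other keeps them.

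**3. What removal could do (assumed inputs)**

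The documents give no rate of non-compliance by arm and no prognosis for those who leave. The following are assumptions: no true drug effect, 120 per arm, 3-year recurrence-free survival 64% overall in both arms, and 20% of patients with a poorer prognosis.

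Analytic check with double hazard in the poor-prognosis group. Let x be 3-year survival in the others:
- 0.8x + 0.2x² = 0.64 gives x = 0.683; the poor-prognosis group has x² = 0.467.
- If all of the poor-prognosis group leave entecavir and none leave TDF, entecavir appears as 68.3% against 64%. The apparent TDF/entecavir hazard ratio is about ln(0.64)/ln(0.683) = 1.17.
- If half leave entecavir, they remain 0.1/0.9 = 11.1% of that arm. Survival is 0.889 × 0.683 + 0.111 × 0.467 = 0.659, and the ratio is about ln(0.64)/ln(0.659) = 1.07.

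Simulation with 2-year accrual, 7 years in total and the log-rank test at two-sided 0.05. Repeat runs differ slightly, so small ranges are shown:

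| Who leaves (poor-prognosis patients only) | Hazard multiple | Hazard ratio, TDF/entecavir | Type I error |
|---|---|---|---|
| Nobody | 2 | 1.00 | about 5% |
| 24 patients, split evenly | 2 | 1.00 | about 5% |
| 24 patients, split 60:40 | 2 | 1.03 | 5–6% |
| Half, entecavir only | 2 | 1.06 | about 6% |
| Half, TDF only | 2 | 0.93–0.94 | 6–7% |
| Half, entecavir only | 3 | 1.10 | 8–9% |
| All, entecavir only | 2 | 1.15–1.16 | 11–12% |

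A simpler calculation agrees in scale. Suppose 10% of one arm is excluded, with event risk r times the arm's 36%. The remaining event rate is (0.36 − 0.10 × r × 0.36)/0.90. For r = 1.25, 1.5 and 2, apparent 3-year survival is 65%, 66% and 68%, a spurious gain of 1 to 4 points.

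**The case against.** **A milder reading.** The sentence says excluded from the study, not from the analysis, and the section written for non-adherence is the natural one to govern. The sentence might then be loose wording for withdrawal from study procedures. The document does not say so. Even on that reading, ending follow-up for non-compliers clashes with the promise to follow treatment dropouts. The conflict stands either way.

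**The Discussion as an exit rule.** A reader might infer that a request to convert formally removes a patient. The sentence is a disclosed limitation about what some patients may do. It sets no analysis exclusion, and it should be reworded rather than removed.

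**Who leaves.** A reader might infer that leavers will be those with poor viral response. The documents do not show this. They provide a drug change within the protocol for such patients and permit treatment of recurrence, and they call neither of these non-compliance.

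**The Outcomes sentence.** It follows the overall-survival definition and does not use the word censored, so it is weaker evidence for the primary outcome. The non-adherence section covers loss to follow-up generally and carries the argument.

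**The magnitude.** The largest figures assume that only poor-prognosis patients leave and that they leave one arm only. In the most extreme case, 24 patients leave one arm, which is the whole trial's planned loss. Balanced exits give essentially no bias. This objection stands and limits what can be claimed about size.

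**Conclusion.** The contradiction is real and rests on the text alone. One section removes participants on post-randomisation behaviour, another keeps them, and nothing says which prevails. Followed literally, the eligibility sentence would give a per-protocol comparison labelled intention-to-treat. It decides who enters the primary analysis, so it needs correcting.

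The size of the harm is not established. With assumed inputs and no true effect, it ranges from none (balanced exits: hazard ratio about 1.00, type I error about 5%) to a hazard ratio of about 1.16 with type I error of about 11% in the extreme one-arm case. The direction depends on which arm loses patients. A reader might infer that the plan favours one drug or that its error rate is doubled; the documents support neither claim.

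**What to change.** 1. **Eligibility criteria:** delete the sentence, or limit it to a judgement made before randomisation that a candidate is unlikely to comply or attend.
2. **Non-adherence section:** state that all randomised patients are analysed in the allocated arm, and that non-compliance, a change of drug or a request to convert ends neither follow-up nor inclusion in the analysis. Patients who withdraw consent or are lost are included up to last contact. A demand to follow everyone to death or study end would go too far, because the retention section gives participants the right to withdraw at any time.
3. **Discussion:** keep the limitation, but reword it so that a conversion request does not trigger exit from follow-up or analysis.
4. **Compliance-based set:** if wanted, label it a per-protocol sensitivity analysis.

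The cost is a wording amendment sent to the ethics committee and the registry. The sample size and treatment are unchanged, and follow-up of dropouts is already promised. Recruitment began in July 2021, so the team should also check whether anyone has already been removed under the sentence and restore their data where consent allows.

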### Recruitment

Eligible inpatients of the Guangxi Medical University Cancer Hospital, the First People’s Hospital of Qinzhou, and the Second Affiliated Hospital of Guangxi Medical University will be included into this study. The benefits and safety of the treatment plan in this study for patients will be explained to secure continuous recruitment.

### Who will take informed consent?

Informed consent will be completed by the participants during the perioperative period after they get understand to the benefits and safety of this study, and it will be delivered to the trained research staff in person.

### Additional consent provisions for collection and use of participant data and biological specimens

There are no additional consent provisions since the participant data will only be used for the purpose of the current trial, but not for future use in ancillary studies. Blood will be collected to assess liver function, renal function, HBV DNA levels, and other outcomes in the trial.

### Interventions

#### Explanation of the choice of comparators

Entecavir and TDF are standard first-line treatments for individuals chronically infected with HBV in clinical practice, and patients can obtain both drugs at relatively low prices. Although the short-term efficacies of either monotherapy with entecavir or TDF in preventing viral reactivation and HCC have been certified, the long-term efficacies in preventing tumor recurrence for patients with HBV-associated HCC after curative hepatectomy are still controversial. Therefore, this study aims to compare the long-term efficacies of the two monotherapies.

#### Description of interventions

Once the first blood test is positive for HBsAg or HBV DNA, participants will be prescribed 300 mg/day of oral TDF or 0.5 mg/day of oral entecavir for long-term administration. After curative hepatectomy, patients will return to the hospital for follow-up examinations according to standard practices at the study sites.

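### The rules for drug start, entry criteria and envelope opening cannot all be followed in any one order

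*Protocol article*

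**What the plan says.** All references are to the Protocol article.

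- **Drug start.** Description of interventions: "Once the first blood test is positive for HBsAg or HBV DNA, participants will be prescribed 300 mg/day of oral TDF" (or entecavir). The next sentence turns to follow-up: "After curative hepatectomy, patients will return to the hospital for follow-up examinations".
- **Treatment window.** Trial design gives one arm TDF, while "the other will receive entecavir monotherapy during the peri- and postoperative period". The Abstract is narrower and speaks of patients "who receive entecavir or TDF after curative resection".
- **Qualifying test.** Eligibility criteria: "they must have tested positive for HBsAg and/or HBV DNA at admission". Table 1 (Outcomes) lists a hepatitis B test at the preoperative visit.
- **Surgery and histology as entry criteria.** Eligibility criteria: "they must have undergone curative hepatectomy at one of the study sites", and "their diagnosis of HCC must have been confirmed by postoperative histopathology". The same section adds: "Curative resection is defined based on intra- and postoperative criteria".
- **Prior therapy.** Eligibility criteria exclude patients on anti-HBV treatment before enrolment, and name both study drugs among the examples.
- **Allocation.** Implementation has the envelope opened by a designated person once eligibility is confirmed.
- **Blinding and analysis set.** Investigators and participants know the arm (Who will be blinded). The analysis follows intention-to-treat (section on protocol non-adherence and missing data).

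**The concern.** A randomised comparison needs a fixed order: consent, eligibility, allocation, first arm-specific dose. Here the dose is tied to a test at admission, while eligibility depends on facts that exist only after the operation. A site has to break one rule or another, and the text does not say which.

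The two ways of breaking it carry different risks.

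- **Allocation before surgery.** Whether the resection was curative, and whether the tumour was HCC, are settled after randomisation by people who know the arm. Part of the curative definition is judged postoperatively. If a failed criterion leads to removal, the compared groups are no longer those that were randomised.
- **Allocation after surgery.** Any TDF or entecavir taken between the admission test and the envelope was chosen by someone and not by the randomisation. Where enrolment follows that first dose, the patient also meets the prior-therapy exclusion.

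**Working it through.** This is a question of order, so the check sets the rules side by side.

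**Step 1. When each condition can first be met**

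| Event | Source | Earliest time |
|---|---|---|
| Positive HBV test (T) | Eligibility criteria; Table 1 | Admission, before surgery |
| Assigned drug prescribed (D) | Description of interventions | At T |
| Curative hepatectomy judged (S) | Eligibility criteria | During and after surgery |
| Histology (H) | Eligibility criteria | After surgery |
| Eligibility confirmed (E) | Needs S and H | After H |
| Envelope opened (R) | Implementation | After E |

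**Step 2. The implied order.** Eligibility criteria and Implementation give T, then S and H, then E, then R. An arm-specific drug cannot be assigned before R, so D must come after S and H. Description of interventions puts D at T. Both cannot hold while T is at admission.

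**Step 3. Readings that might rescue the text**

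- *The patients being prescribed drug are already randomised.* Then R comes before surgery, and the surgery and histology criteria were not confirmed before the envelope was opened. The conflict moves to Eligibility criteria and Implementation.
- *The first test means the first after surgery.* Table 1 has no hepatitis B test on postoperative day 5; the next one is at one month. Treatment starting then would not fit the perioperative window in Trial design, nor the admission test in Eligibility criteria.
- *Drug start coincides with enrolment.* Criteria for discontinuing or modifying allocated interventions does refer to the medication in use at enrolment. It does not date enrolment relative to surgery. If enrolment is at admission, the entry criteria fail; if it is after histology, the test-triggered start fails.
- *Consent fixes the order.* Consent is placed in the perioperative period, which spans the operation and does not settle it.

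**Step 4. Does any stated number change?** The sample size section assumes 3-year recurrence-free survival of 64% and 79%, 90% power, two-sided alpha 0.05, two years of enrolment and five of follow-up.

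- Hazard ratio = ln 0.79 / ln 0.64 = 0.528.
- Events (Schoenfeld) = 4 × (1.960 + 1.282)² / (ln 0.528)² ≈ 103.2, so 104.
- With exponential survival, uniform accrual over two years and five further years of follow-up, the mean event probability is about 0.482. Then 104 / 0.482 ≈ 215.7, so 216, or 108 per group.
- 216 / 0.90 = 240.

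The plan's figures reproduce. None of the inputs depends on the order of dose, surgery and allocation.

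**Step 5. Can the bias be sized?** No. The documents give no rate of non-curative resection, no rate of histology other than HCC, and no interval from first test to allocation.

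**The case against.** The strongest reply is that preoperative dosing is inferred. Description of interventions gives a trigger and does not mention surgery in that sentence. The sentence after it concerns follow-up visits, which come after surgery whenever the drug starts, so sentence order proves little. Perioperative is not the same as preoperative, the Abstract is only shorthand, and the participant flowchart (Fig. 1), which is not shown, may give the intended sequence. All of this stands as a limit on certainty. It does not remove the conflict: the admission test together with the perioperative window makes the inference strong, and each alternative in the working breaks another stated rule. A flowchart would not change the wording of those rules.

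Three stronger readings are tempting but unsupported.

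- *Patients who fail the surgery or histology criteria are removed after randomisation.* The document does not say so, and it states intention-to-treat. Eligibility criteria do list one exclusion that can apply only once treatment has begun (non-compliance or incomplete follow-up), so the list is not purely a gate before allocation. That exclusion does not concern curative status.
- *Study drug makes every patient ineligible under the prior-therapy exclusion.* This follows only if enrolment comes after the first dose, and the passage on medication at enrolment can be read otherwise.
- *Patients have actually been dosed before allocation.* The text shows rules in conflict and says nothing about what sites have done.

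**Conclusion.** The point holds as an inconsistency between stated rules. Trial design, Eligibility criteria, Description of interventions and Implementation cannot all be followed. The conclusion rests on reading the qualifying test as preoperative, which Eligibility criteria and Table 1 support.

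The harm is conditional on which rule sites break in practice. No number of patients and no direction of bias can be given, and the sample size stands. It should be fixed because the correction is cheap and closes a route to arm-aware exclusion in an open-label trial. Confidence is medium: the textual conflict is clear, but the practice behind it is unknown.

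**What to change.** Perioperative treatment appears to be intended, so put allocation before it:

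1. State that consent and envelope opening precede the first study dose.
2. Restrict the entry criteria to what is known before surgery. Move curative status and histology to descriptions recorded after surgery.
3. Define enrolment, in the prior-therapy exclusion, as randomisation.
4. Keep every randomised patient in the primary intention-to-treat analysis. State in advance how recurrence-free survival is counted for those left with residual tumour or found not to have HCC.
5. Add a sensitivity analysis in histologically confirmed, curatively resected HCC.
6. Record the first-dose date. The randomisation date is already the survival origin, and the surgery date is already needed for the 24- and 48-week outcomes and the 3-month switching rule. For patients already recruited, report how many took a first dose before randomisation.

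The cost is amended wording in Trial design, Eligibility criteria, Description of interventions and Implementation, one added date on the case report form, and one sensitivity analysis. Sample size and follow-up do not change. The downside is that a few randomised patients without resected HCC may slightly dilute the primary comparison. The alternative, allocating after histology and starting drug only then, would avoid that dilution but delay antiviral cover in HBV-positive surgical patients.
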